##### Adverse Events

Adverse events will be assessed through participant self-reporting. The number of falls, hospitalizations in the last 5 months, and emergency room visits will be recorded for participants during the study.

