## Methods

### Study Design

The study protocol adhered to the SPIRIT guidelines (Checklist 1) [50]. The Ethics Committee of the School of Nursing, Jilin University, approved the ethical clearance for the project (2023122001). The trial was registered in the China Clinical Trial Registry on March 25, 2024 (ChiCTR2400082225). This is a multicenter, assessor-blinded, 18-week, two-arm, parallel-group, randomized controlled trial examining the effects of an MTM-based sedentary lifestyle change intervention for older adults on SB, PA, and health outcomes compared with usual education.

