### Study Measurements

#### End Points

The duration of the intervention is 6 weeks with 12 weeks of follow-up. Outcome measures were collected at baseline T1, end of intervention (week 6) T2, week 12 (T3), and week 18 (T4; Figure 2). The primary endpoint is the change in self-reported ST (total ST and SB characteristics, such as screen-based ST, longest continuous ST, and number of sedentary bouts ≤30 min). Secondary endpoints include the changes in step count (steps/d), time spent in LPA (min/wk), time spent in MVPA (min/wk), the Short Physical Performance Battery (SPPB) score, blood pressure, Measuring Change in Physical Activity Questionnaire (MCPAQ) score, waist circumference, BMI, and quality of life (SF-12v2 score) (Table 2).

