**Figure 2. F2:**
[figure not shown]
CONSORT flow diagram.

**Table 2. T2:** Participant schedule of enrollment, interventions, and assessments.

	Study period				
	Enrollment	Baseline assessment/allocation	Post allocation		
Timepoint	T0	T1	T2 6 wk	T3 12 wk	T4 18 wk
Eligibility screen	×				
Informed consent	×				
Allocation		×			
Interventions					
CON group					
INT group					
Assessments					
Sociodemographics		×			
Primary outcomes					
Sedentary time (total sedentary time and sedentary behavior characteristics)		×	×	×	×
Secondary outcomes					
Step count (Omron HJ-204)		×	×	×	×
Time spent in LPA/MVPA (IPAQ-S-C)		×	×	×	×
Measuring Change in Physical Activity questionnaire (MCPAQ)		×	×	×	×
Physical function (SPPB)		×	×	×	×
Quality of life (SF-12)		×	×	×	×
BMI		×	×	×	×
Waist circumference		×	×	×	×
Blood pressure		×	×	×	×

a SF-12: Short-Form Health Survey-12.

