### Adverse Events and Audit

The research team will collect, report, and assess adverse events to determine their severity and whether they are related to this trial. Serious adverse events and reactions will be reported to the Ethics Committee and appropriate measures will be taken (if present). Audits will be conducted by the School of Nursing, Jilin University.

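### The 5-month look-back for hospitalisations is longer than the 18 weeks from allocation to the last visit, so admissions before randomisation can enter the on-study count

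*Protocol article*

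**What the plan says.** The Adverse Events section of the protocol article sets the method, "Adverse events will be assessed through participant self-reporting", and then the counts: "The number of falls, hospitalizations in the last 5 months, and emergency room visits will be recorded for participants during the study". As punctuated, the 5-month window belongs to hospitalisations only. No visit is named for the question, and the assessment schedule in Table 2 has no adverse event row.

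The length of the study is given three times, consistently:

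- Study Design describes an "assessor-blinded, 18-week, two-arm, parallel-group, randomized controlled trial".
- End Points says: "The duration of the intervention is 6 weeks with 12 weeks of follow-up". It places the last assessment, T4, at week 18.
- Table 2 puts allocation at T1, in the column headed "Baseline assessment/allocation", and labels T2, T3 and T4 as post-allocation at 6, 12 and 18 weeks.

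The later section Adverse Events and Audit adds: "The research team will collect, report, and assess adverse events to determine their severity and whether they are related to this trial". It gives no rule on when an event must have begun to be counted.

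**The concern.** The sentence on hospitalisations names two periods, the last 5 months and the study itself, and on the article's own figures these differ. A look-back longer than the time since allocation takes in time when no participant had yet been assigned to an arm. An admission in that time cannot be an effect of the allocated programme.

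Hospitalisation is one of only three safety counts that the article names. The participants are aged 65 or over, and the programme moves them towards more intense activity. With 60 participants enrolled, admissions may be few, so one or two misdated ones could change the safety summary. Admissions before allocation would raise the count in both arms and pull any true difference towards no difference.

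**Working it through.** **Inputs**

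- Look-back for hospitalisations: 5 months (Adverse Events).
- Time from allocation to last visit: 18 weeks (Study Design, End Points, Table 2).
- Assumption: week 0 is the day of allocation. Table 2 supports this by labelling the visits as post-allocation.
- Assumption: the question is asked once, at T4. The article names no visit.

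**The plan's own figure.** 6 weeks of intervention + 12 weeks of follow-up = 18 weeks = 126 days. In months, 126 / (365.25/12) = 4.14. The stated 18 weeks is reproduced, and it is less than 5 months.

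**Length of the look-back.** 5 × 365.25/12 = 152.2 days, and 152.2/7 = 21.74 weeks.

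**Overhang before allocation at T4.** Overhang = window − 18 weeks. Share = overhang / window.

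| Definition of 5 months | Window (weeks) | Overhang (weeks) | Share of window |
|---|---|---|---|
| Average month (152.2 days) | 21.74 | 3.74 | 17% |
| Shortest calendar run (150 days) | 21.43 | 3.43 | 16% |
| Longest calendar run (153 days) | 21.86 | 3.86 | 18% |
| Five 4-week months (140 days) | 20.00 | 2.00 | 10% |

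The overhang is positive under every definition.

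**If the question were asked earlier.** With the average month the overhang would be 21.74 − 12 = 9.74 weeks at T3 and 21.74 − 6 = 15.74 weeks at T2. These figures are conditional on a schedule that the article does not state.

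**Effect on the count (illustration).** Assume a constant admission rate with no treatment effect. A 21.74-week window then gives 21.74/18 = 1.21 times the count of an 18-week window (20/18 = 1.11 with 4-week months).

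**Effect on a comparison of arms (illustration).** Assume equal background rates and a hypothetical true rate ratio of 2.0 after allocation. The observed ratio at T4 is (3.74 + 2 × 18) / 21.74 = 39.74/21.74 = 1.83. With 4-week months it is (2 + 36)/20 = 1.90. The ratio of 2.0 is chosen only to show the size of the dilution; the article gives no expected rate.

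**What would remove the overhang.** A gap of about 3.7 weeks or more between allocation and the start of the 18-week clock would do so. No such gap is stated.

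**The case against.** The strongest reply is that the sentence also limits the recording to the study, so a reader may take the 5 months as a rounded description of participation as a whole, including the enrolment point T0 that Table 2 shows before T1. On that reading nothing outside the study is meant to be counted. The team will also judge whether each event is related to the trial, and an admission before allocation would presumably be judged unrelated. Adverse events are neither primary nor secondary endpoints, and Statistical Analyses names no comparison of event counts between arms.

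Much of this stands, and it limits the point. Three stronger readings are tempting, and the article does not support them:

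- **That admissions before randomisation are counted as on-study events.** The text neither includes nor excludes them. It only allows them in.
- **That the whole safety look-back is 5 months.** The window is attached to hospitalisations. Falls and emergency room visits carry none.
- **That most of the window lies before allocation, or that admissions are counted twice.** Either would need the same question at T2 or T3, and no visit is given. A single question at the end fits a 5-month window better.

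What does not stand is the claim that the mismatch is already resolved. Counting enrolment as part of the study does not help, because an admission before allocation still cannot be an effect of the assigned arm. A relatedness judgement classifies an event but does not take it out of the recorded number. Nor is this merely detail that an article leaves to a fuller document: the article states a specific window, and that window conflicts with its stated duration.

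**Conclusion.** The point holds in a narrow form. The look-back for hospitalisations exceeds the period from T1 to T4 by about 3.7 weeks (3.4 to 3.9 weeks with calendar months, 2 weeks with 4-week months). Followed as written at week 18, it can admit hospitalisations from before randomisation.

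This rests on two assumptions, that week 0 is the day of allocation and that the question is asked at T4. An earlier question would widen the overhang; an unstated gap between allocation and week 1 would shrink it. Randomisation balances earlier admissions in expectation, so the result is inflated counts and modest dilution, with no systematic tilt towards either arm. Severity is low.

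**What to change.** Reconcile the window with the study period: define the hospitalisation count as admissions from randomisation (T1) to T4, ascertained in the same way in both arms.

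The article reports data collection as complete by May 2025, so the change falls mainly on the analysis and the report. Where admission dates were kept, exclude those before T1. Where they were not, state the recall window actually used and say that it includes time before randomisation. Nothing in this point requires a change to falls or emergency room visits.

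The cost is one sentence and some recoding by date. No new data are needed.

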### Sample Size Calculation

The sample size was calculated using G*Power software (version 3.1.9.6) [60]. The sample size estimation refers to the standardized deviation of the self-reported ST among community-dwelling older adults obtained from a similar previous study [42]. A total of 48 older adults (24 per group) will be required to detect the effect size of 0.84, with a power of 80% (1−*β*=0.80) and a level of significance of 5% (*α*=.05, 2-tailed) by unpaired *t*-test. Using an SD of 142.98 minutes per day and an expected reduction of 120 minutes per day self-reported sitting time, a sample size of 24 patients per arm is needed. Taking a dropout of 15% into consideration, we will have at least 56 participants in our study.

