### Study Interventions

Using the MTM as a framework and based on the review of relevant guidelines and literature, the sedentary lifestyle intervention program for community-dwelling older adults was developed (Table 1). Multimedia Appendix 1 shows the mapping of the sedentary lifestyle change interventions in the MTM, and Multimedia Appendix 2 shows the mapping of the sedentary lifestyle change interventions in the “staircase approach.” Participants in the intervention group will receive a sedentary lifestyle modification intervention based on the MTM and the staircase approach. Participants in the usual care group will receive a group education session (non-stepwise) on changing sedentary lifestyles and will be given a healthy behavior manual, an activity diary, and a pedometer.

**Table 1. T1:** The multi-theory model (MTM)–based sedentary lifestyle intervention program for community-dwelling older adults.

Timing and interventions	MTM constructs	BCTs^a^	Content of interventions	Duration/frequency
Week 1‐2, Phase I				
Discussion of advantages and disadvantages	Participatory dialogue/emotional transformation	Pros and cons	In small groups of 2‐3 people, participants engage in face-to-face communication with health educators to discuss the advantages and disadvantages of sedentary lifestyles and to identify the main factors contributing to sedentary lifestyles, concerns regarding behavior change and the home environment in order to provide personalized advice.	20 min/group
Thematic session on sedentary behavior change	Behavioral confidence	Information about health consequences Credible sources Instruction on how to perform the behavior Problem solving	This session will focus on the recognition and prevalence of SB^b^, the harms of being sedentary, the benefits of reducing sitting time, etc Peer sharing: sharing the adverse effects of long-term SB through the experiences of others, video cases, etc Recommendations for reducing SB—interrupting or replacing SB with standing or LPA^c^, household domain physical activity in different settings where it occurs, etc Give personalized guidance on the main causes of SB for each older adult. Co-discuss the barriers that participants may encounter during the process of SB change and provide practical solutions (after discussion of advantages and disadvantages).	60 min

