### Statistical Analyses

Data analyses follow intention-to-treat principles, using generalized estimating equation models to assess differential changes in the outcome variables between the 2 groups from baseline to 12 weeks (group×time interaction), with adjustment for potential covariates as appropriate (ie, baseline group differences at 2-sided *P*<.25). Effect sizes for continuous outcome variables were estimated using Cohen *d* statistic based on between-group mean differences from baseline T1 to T2, T3, and T4 end points with cutoffs set at 0.2 (small), 0.5 (medium), and 0.8 (large) [62]. Each generalized estimating equation model includes the main effects of group (intervention vs control), time (T2, T3, T4 vs baseline), and 2-way interaction effects (group×time). The group difference in the change from baseline to 6, 12, or 18 weeks between the 2 groups is verified when the 2-way interaction effects (group×time) was statistically significant. All statistical analyses are 2-sided and performed using IBM SPSS 25.0 software. *P* values <.05 is considered statistically significant.

Continuous variables that conform to normal distribution will be expressed as mean (SD) using an independent samples *t* test. Continuous variables that are not normally distributed and ranked variables will use the Mann-Whitney *U* test, expressed as median (M) and quartiles (P₂₅-P₇₅). Categorical table variables will be statistically described by frequency and percentage (%) using *χ*² test or Fisher exact test.

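### The stated 80% power carries over to the planned change-from-baseline analysis only under two unstated conditions; a baseline-adjusted model removes one, and the text must settle the other

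*Protocol article*

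**What the plan says.** Under Sample Size Calculation, the protocol article takes its SD from an earlier study and describes it as the "standardized deviation of the self-reported ST among community-dwelling older adults". It then plans for 24 per group "to detect the effect size of 0.84" by a two-tailed unpaired t-test at the 5% level, "Using an SD of 142.98 minutes per day and an expected reduction of 120 minutes per day self-reported sitting time". No comparator is attached to the reduction, and no change is stated for the control arm. The section ends: "Taking a dropout of 15% into consideration, we will have at least 56 participants in our study".

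Under End Points, the primary endpoint is the change in self-reported sedentary time. Under Statistical Analyses, it is tested by a generalized estimating equation with group, time (each later visit against baseline) and their interaction. Covariates enter only where the arms differ at baseline at P<.25.

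Under Study Interventions, controls receive a group education session on changing sedentary lifestyles and "will be given a healthy behavior manual, an activity diary, and a pedometer". The Results section reports 60 recruited and data collection complete.

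**The concern.** An unpaired t-test needs two inputs: the difference between arms in the quantity compared, and the SD of that quantity. Here the quantity analysed is change from baseline. The article supplies a reduction without a comparator and an SD that reads as the spread of sedentary time itself. Neither is plainly the input that the test requires.

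The first matters because the controls are not untreated. They are advised on the same behaviour and given two self-monitoring tools, and the outcome is self-reported. If 120 min/day is what the intervention arm is expected to lose, it equals the between-arm difference only when controls do not change.

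The second matters because the SD of a change depends on how strongly baseline and follow-up correlate, and the article does not give that correlation.

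The risk lies in interpretation. A non-significant result could be read as evidence of no effect from a trial with 80% power, when the power of the analysis actually run is unknown and may be well below that.

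**Working it through.** **Inputs from the article:** difference 120 min/day; SD 142.98 min/day; two-sided alpha 0.05; 24 per arm; dropout 15%; 60 enrolled. **Assumptions, not in the article:** the correlation r, the change in controls, and equal SDs at baseline and follow-up.

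**1. The plan's own figure.** d = 120/142.98 = 0.839. With n per arm, the noncentrality is d·√(n/2) on 2n − 2 degrees of freedom. At n = 24 this is 0.839 × √12 = 2.91 on 46 df, and power is 81.2%. At n = 23 it is 79.5%. So 24 per arm reproduces, and it does so by using 120 as the full between-arm difference and 142.98 as the SD of the quantity compared.

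**2. If 142.98 is an SD of levels and 120 is a true between-arm difference.** For the unadjusted change contrast, SD = 142.98 × √(2(1 − r)). With baseline as a covariate, SD = 142.98 × √(1 − r²).

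| r | SD of change | Power, change, 24/arm | Power, change, 25.5/arm | Power, baseline-adjusted, 24/arm |
|---|---|---|---|---|
| 0.3 | 169.2 | 67% | 69.9% | 85% |
| 0.4 | 156.6 | 74% | 76.5% | 87% |
| 0.5 | 143.0 | 81% | 83.6% | 91% |
| 0.6 | 127.9 | 89% | 90.7% | 94% |
| 0.7 | 110.8 | 96% | 96.7% | 98% |

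The 25.5 per arm is 60 × 0.85 = 51 completers, halved. At r = 0.5 the factor √(2(1 − r)) is 1, so the change SD equals the level SD. Below 0.5 the plan is optimistic; above 0.5 it is conservative. The adjusted SD never exceeds 142.98, so its lowest power at 24 per arm, at r = 0, is about 81%.

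**3. If 120 is the reduction in the intervention arm.** The difference is 120 minus the control reduction, with the SD kept at 142.98.

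| Control reduction (assumed) | Difference | d | Power, 24/arm | Power, 25.5/arm |
|---|---|---|---|---|
| 0 | 120 | 0.839 | 81% | 84% |
| 20 | 100 | 0.699 | 66% | 69% |
| 30 | 90 | 0.629 | 57% | 60% |
| 40 | 80 | 0.560 | 48% | 50% |

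**4. Both together.** With a difference of 90 and the unadjusted change contrast at 24 per arm, power is 44% at r = 0.3 and 79% at r = 0.7.

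**5. Dropout.** 48/0.85 = 56.5, so 57 (58 for equal arms). The stated 56 matches 48 × 1.15 = 55.2 rounded up. At 56, 47.6 completers are expected; 24 and 23 per arm give 80.4%.

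**The case against.** An effect size for an unpaired t-test is by definition a between-group quantity, so 120 may simply be loosely worded shorthand for the between-arm difference. That is fair. A reader might infer that 120 is a within-arm change wrongly used as a contrast, but the article never says so. The wording leaves the point open; it does not prove an error.

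A reader might also infer that an SD of levels must overstate the power for change. It need not: above r = 0.5 it understates it. Nor does the article say outright whether 142.98 is an SD of levels or of change, and the study it comes from is not available here.

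The control reductions of 20 to 40 min/day are illustrations. Nothing in the article shows them to be likely, so it would be wrong to say that the true power is 50 to 70%.

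The dropout figure does not make the trial too small. The text sets a minimum, and the 60 enrolled leave 51 after 15% loss, above the 48 required.

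Finally, the Strengths and Limitations section concedes that the modest sample may limit power. That is a general caution and does not tell the reader that the 80% depends on r and on what controls do.

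What remains is a mismatch between the sized test and the planned one, and two conditions that the article leaves unstated.

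**Conclusion.** The concern holds in limited form. The calculation is internally correct, but it supports the planned group-by-time analysis only if 120 min/day is a between-arm difference in change and, should 142.98 be an SD of levels, only if r is about 0.5 or more. Over r from 0.3 to 0.7 the power of the unadjusted change contrast runs from 67% to 96% at 24 per arm. If 120 is the reduction in the intervention arm, modest control improvement takes power from 81% to between 66% and 48%, and recruiting 60 restores only 2 to 3 percentage points after 15% loss. All these ranges rest on assumed values of r and control change.

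The two conditions differ in how they can be met. Adjusting for baseline removes the dependence on r. No choice of model restores a between-arm difference that is smaller than planned, so that part needs a clear statement. The dropout figure is a rounding remark only.

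**What to change.** 1. In Statistical Analyses, estimate the primary effect with a baseline-adjusted model: sedentary time at the follow-up visits as the outcome, with baseline sedentary time as a covariate alongside group, time and their interaction. Include the covariate whatever the baseline P value. The baseline is already collected, so this needs no new data. It does change the analysis text, so it should be recorded before outcomes are examined by arm. If that has already happened, report it beside the planned analysis and label it as added later.
2. In Sample Size Calculation, state that 120 min/day is the between-arm difference in change or, if it is not, give the assumed control change. State whether 142.98 is an SD of levels or of change.
3. Replace the single 80% with power for the 60 enrolled (about 51 after 15% loss), over values of r on both sides of 0.5 and over a stated range of control change.
4. Optionally, correct 56 to 57.

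The cost is one revised paragraph and one revised model specification, with no further recruitment. The power reported may be less favourable if 120 proves not to be the between-arm difference.

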### Randomization and Blinding

Participants will be randomized in a 1:1 ratio into a behavioral intervention group, which receives a staircase MTM-based SB change intervention and a usual care group, which receives recommendations for reducing SBs. Randomization will be stratified by center, and each center will be grouped by age 65 to 75 and ≥75 years (as older adults aged ≥75 y are more likely to experience mobility impairment due to chronic conditions, resulting in higher ST compared to those aged 65‐75 y) [19,61]. Using a permuted block randomization, with a block size of 4, allocation sequences will be generated online using a website (www.randomizer.org) by an independent professional who will not be involved in subject recruitment, intervention implementation, or outcome assessment for this study, and investigators will be informed of group assignment by telephone.

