### Participants

Participants for this study were recruited through posters and leaflets distributed at 2 community health service centers in Changchun City, Jilin Province, China, from March 2024 to October 2024. All participants signed informed consent before the baseline outcome assessment. The following are the inclusion and exclusion criteria for participants:

Inclusion criteria:

Older adults aged ≥65 years.Residents living in the community for ≥6 months.Sedentary lifestyle (ie, more than 6 h of time awake spent in a sitting or reclining posture per day and PI: MVPA ≦150 min/wk) for at least 6 months.Able to walk 100 m without assistance.Informed consent and voluntary participation in this study.

Exclusion criteria:

Severe physical illness or long-term bedridden.Unable or unwilling to communicate with researchers.Participating in other PA or SB intervention programs.Severe cardiovascular and cerebral vascular diseases that require restriction of activities.Severe muscle weakness, skeletal diseases, or deformities that lead to restriction of PA.Depression, schizophrenia, and other psychiatric disorders or dementia that led to severe cognitive impairment.History of central nervous dysfunction, such as mild hemiplegia, spinal cord disease, and cerebral ataxia.

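### The two age strata for randomisation both contain age 75, so the list for a 75-year-old is undefined, and the strata are not fixed as terms in the analysis model

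*Protocol article*

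**What the plan says.** Under Randomization and Blinding, the article states "Randomization will be stratified by center" and then that "each center will be grouped by age 65 to 75 and ≥75 years". The reason given compares the same two bands. For the upper band it reads "as older adults aged ≥75 y are more likely to experience mobility impairment due to chronic conditions"; the group it is set against appears later in that sentence, in the words "resulting in higher ST compared to those aged 65‐75 y". Assignment is by permuted blocks: "Using a permuted block randomization, with a block size of 4". The sequences come from an independent professional who takes no part in recruitment, intervention or outcome assessment, and investigators learn the assignment by telephone.

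Under Participants, recruitment used "leaflets distributed at 2 community health service centers", and the age criterion is "Older adults aged ≥65 years" with no upper limit, so people aged 75 are eligible.

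Under Statistical Analyses, the GEE models contain group, time and their interaction. Further covariates are added when the groups differ at baseline at two-sided P below .25. Neither center nor age band is named as a model term. The Results section reports that recruitment (60 participants) and data collection were complete by May 2025.

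**The concern.** Strata have to be mutually exclusive, because each one corresponds to its own allocation list. Here a 75-year-old meets the definition of two lists at the same center, and the article gives no rule for choosing between them. A reader cannot reproduce the stratification for these participants. Anyone who later derives the stratum from recorded age has to guess, and may put them in a different stratum from the one used at randomisation.

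The second effect becomes concrete once the strata enter the analysis, as they normally should after stratified randomisation. The stated covariate rule makes their inclusion depend on observed imbalance. Stratification is designed to keep these factors balanced, so the rule will tend to leave out the very factors that shaped the allocation. The article itself expects the older band to have more sedentary time, so age band is presented as prognostic for the primary outcome.

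**Working it through.** **1. Membership of the bands as written.** Inputs: lower band 65 ≤ age ≤ 75 and upper band age ≥ 75 (Randomization and Blinding); eligibility age ≥ 65 (Participants). Each whole-year age from 65 to 99 was checked against both bands:

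- 65 to 74: lower band only.
- 75: both bands.
- 76 to 99: upper band only.

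Either non-overlapping version (65-74 with ≥75, or 65-75 with >75) puts every age in exactly one band. It yields 2 centers × 2 age bands = 4 separate lists.

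**2. Does the rationale settle the boundary?** Its first half uses ≥75, which alone would suggest 65-74 for the younger group. Its second half gives the comparison group as 65-75. The overlap is therefore repeated, not resolved, and 65-74 appears nowhere in the article.

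**3. How many participants?** The age distribution is not given. Assuming an even spread over whole years:

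- ages 65-84 (20 values): 60/20 = 3.0 participants aged 75 (5%);
- ages 65-90 (26 values): 60/26 = 2.3 participants (about 4%).

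**4. Predictability of blocks of 4.** There are six arrangements of two A and two B. In AABB and BBAA the last two assignments are determined by the earlier ones; in the other four arrangements only the last is. The expected number determined is (2×2 + 4×1)/6 = 8/6 = 1.33 of 4, or one third. The best guess is right with probability (1/2 + 2/3 + 2/3 + 1)/4 = 2.83/4 = 71%. These figures hold for any fixed block of 4, whether or not the strata overlap, so they do not measure harm from the overlap.

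**5. What the overlap could add at most.** Suppose someone knew the block size, tracked both lists and was free to choose between them (lists independent, positions random).

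- Full choice of arm needs both lists determined and pointing to opposite arms: 1/3 × 1/3 × 1/2 = 1/18, about 6%. Over 2.3 to 3 people that is 0.13 to 0.17 of a participant.
- Steering toward one preferred arm needs at least one list determined in that direction: 1 − (5/6)² = 11/36, about 31%, against 1/6, about 17%, with a single list. The increment is 5/36, about 14 percentage points, or 0.3 to 0.4 of a participant over 2.3 to 3 people.

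**6. Sample size.** With d = 120/142.98 = 0.839, two-sided alpha 0.05 and power 0.80, the two-sample t-test needs 23.29, so 24 per group (power 0.812). The stated 24 per group reproduces, and it does not depend on the strata.

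**The case against.** The strongest reply is that this is a boundary-wording slip in a condensed article. Several parts of that reply stand.

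- A reader might infer that the stratification rule as a whole cannot be applied. It can, for every age except 75. If age was taken exactly from date of birth, 65 to 75 could be read as ending on the 75th birthday, and the bands would then share only a single point. The article does not say how age was computed, so this reading is possible but not established.
- A reader might infer that recruiting staff could pick the list, and so the arm. The article does not support this. An independent professional generates the sequences, nothing says the person requesting an allocation assigns the stratum, and nothing says recruiting staff knew the block size. Deliberate steering would need all of that and would still concern only a few people.
- A reader might infer from the ≥75 wording that the intended bands were 65-74 and ≥75. The same sentence also says 65-75, so the document does not settle it.
- Adjusting for stratification factors is a separate principle, and the planned models do not include the stratum, so no stratum is mis-derived under the plan as it stands.

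The last point is fair but does not remove the need for action. The plan leaves inclusion of the randomisation strata to a baseline-difference screen. Once they are fixed in the model, the stratum of each 75-year-old must be known. The overlap itself is also unanswered: it is written twice and resolved nowhere.

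**Conclusion.** The overlap is real and narrow. As written, the two bands within each center are not mutually exclusive at age 75, and the article does not define which list such a participant joins. All other ages are unambiguous. The number affected is not stated; 2 to 3 of 60 rests on an even spread of ages.

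There is no evidence that allocation was steered, and assignment within either list is still random. The probable effect on the primary result is small. The practical weight lies in the analysis: center and age band governed the allocation but are not fixed as model terms, and their inclusion depends on a screen at P below .25.

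**What to change.** 1. Restate the age bands as mutually exclusive, using the boundary that was actually applied: 65-74 and ≥75, or 65-75 and >75. Recruitment is over, so this is a matter of record, not a new choice. State also how age was computed.
2. Check the allocation log, record which list each 75-year-old was drawn from, and report it.
3. Name the as-randomised center and age stratum as fixed covariates in the GEE models, independent of the baseline-difference screen, and do not re-derive the stratum from age. Put this in writing before the group comparisons are run; if they have already been run, say so when reporting the adjusted result.

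The cost is one corrected phrase, a log check for a handful of participants, and model degrees of freedom: two if center and age band enter as main effects, three if the four strata enter as indicators (4 − 1 = 3). No new data are needed, and the sample size and power statements do not change.
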